## Abstract

**Background:**

School-based physical education is an important public health initiative as it has the potential to provide students with regular opportunities to participate in moderate-to-vigorous physical activity (MVPA). Unfortunately, in many physical education lessons students do not engage in sufficient MVPA to achieve health benefits. In this trial we will test the efficacy of a teacher professional development intervention, delivered partially via the Internet, on secondary school students’ MVPA during physical education lessons. Teaching strategies covered in this training are designed to (i) maximize opportunities for students to be physically active during lessons and (ii) enhance students’ autonomous motivation towards physical activity.

**Method:**

A two-arm cluster randomized controlled trial with allocation at the school level (intervention vs. usual care control). Teachers and Year 8 students in government-funded secondary schools in low socio-economic areas of the Western Sydney region of Australia will be eligible to participate. During the main portion of the intervention (6 months), teachers will participate in two workshops and complete two implementation tasks at their school. Implementation tasks will involve video-based self-reflection via the project’s Web 2.0 platform and an individualized feedback meeting with a project mentor. Each intervention school will also complete two group peer-mentoring sessions at their school (one per term) in which they will discuss implementation with members of their school physical education staff. In the booster period (3 months), teachers will complete a half-day workshop at their school, plus one online implementation task, and a group mentoring session at their school. Throughout the entire intervention period (main intervention plus booster period), teachers will have access to online resources. Data collection will include baseline, post-intervention (7–8 months after baseline) and maintenance phase (14–15 months after baseline) assessments. Research assistants blinded to group allocation will collect all data. The primary outcome will be the proportion of physical education lesson time that students spend in MVPA. Secondary outcomes will include leisure-time physical activity, subjective well-being, and motivation towards physical activity.

**Discussion:**

The provision of an online training platform for teachers could help facilitate more widespread dissemination of evidence-based interventions compared with programs that rely exclusively on face-to-face training.

**Trial registration:**

Australia and New Zealand Clinical Trials Registry-ACTRN12614000184673. Registration date: February 19, 2014.

**Electronic supplementary material:**

The online version of this article (doi:10.1186/s12889-015-2583-7) contains supplementary material, which is available to authorized users.

## Background

### Purpose

Schools represent an ideal environment for physical activity promotion among youth. They provide access to the majority of the population and have the facilities, trained personnel and curriculum to address public health objectives [1]. Physical education (PE) is the primary vehicle responsible for physical activity promotion in schools and has the potential to provide students with regular opportunities to be physically active. Unfortunately, in many of these lessons students do not engage in sufficient moderate-to-vigorous physical activity (MVPA) to achieve health benefits [2–4]. In this trial we will test the effect of a PE teacher professional development intervention, delivered partially via the Internet, on students’ MVPA during PE lessons. Known as the Activity and Motivation in Physical Education (AMPED) Project, this intervention is also designed to enhance students’ motivation to be physically active during PE lessons and their leisure-time (i.e., outside school hours). If MVPA during PE and leisure time can be increased, youth can be expected to realize a variety of benefits, including enhanced self-concept [5], better quality of life [6], greater engagement at school [7], better academic results [8] and improved physical health [9].

### Overview of previous research

#### Focusing on lesson structure to improve PE lessons provides opportunities for MVPA

Numerous studies have assessed the effect of interventions designed to increase MVPA during PE lessons [3]. These investigations have included large trials in the United States focused on improving PE teachers’ lesson planning and delivery [10, 11]. For example, the Middle School Physical Activity and Nutrition intervention [10] created teacher awareness, helped teachers to design and implement active PE lessons, and developed teachers’ class management skills. Previous interventions focusing on lesson planning and delivery have successfully increased the proportion of time students spent in MVPA during PE lessons. Indeed, a recent meta-analysis [3] found a pooled effect of *d* = 0.6 when comparing the physical activity levels of intervention versus control students. This difference was equivalent to approximately 24 % more MVPA during PE lessons.

#### Student motivation towards PE is associated with MVPA during lessons

Epidemiological evidence suggests that the largest decrease in youth physical activity occurs during early adolescence [12]. This trend parallels age-related declines in adaptive motivation for school and PE, in particular [13]. Few interventions have been specifically designed to motivate students to take advantage of opportunities for MVPA during PE lessons [14]. This omission ignores the evidence that student motivation is an important correlate and likely determinant of MVPA during PE [15]. For example, Lonsdale and colleagues [16] showed that students motivated by autonomous factors (e.g., intrinsic motivation) were 20 % more active than students in the same lessons who were motivated by external factors (e.g., pressure from others). Similarly, Jaakkola and colleagues [17] found that students’ autonomous motivation was a significant correlate of objectively-measured MVPA during PE lessons.

PE teachers can play an important role in motivating children to be actively involved in lessons [18, 19]. Recent studies have shown that PE teachers can be trained to motivate their students more effectively and that these interventions have a positive influence on students’ motivation towards PE [20, 21]. The influence of these interventions on students’ MVPA during PE lessons, however, has received little attention [14, 22].

#### Student motivation towards PE is associated with leisure-time physical activity motivation and behavior

Student motivation towards PE lessons is positively associated with leisure-time MVPA motivation and self-reported PA outside school hours [23]. In addition, interventions with PE teachers that enhance students’ motivation towards PE, also produce increases in leisure-time physical activity intentions [21] and self-reported leisure-time MVPA [20]. There is no evidence, however, regarding the effect of interventions designed to enhance students’ motivation towards PE on objectively-measured PA outside lesson time. Given the general tendency for young people to over-report their MVPA [24] and the evidence that associations between self-reported and objectively-measured MVPA can be poor among youth [25], there is a need to examine intervention effectiveness using objective MVPA measures.

### Theoretical framework for the current study

#### Self-determination theory

Self-Determination Theory (SDT) [26] has been widely applied to a variety of life contexts, including education [27] sport [28], exercise [29] and PE [15, 16, 19, 30, 31]. According to SDT tenets, social-contextual factors (e.g., teachers’ behavior towards students) can affect individuals’ (e.g. students’) motivation by satisfying three key psychological needs: (ii) autonomy, the sense that one is acting in a self-directed manner; (ii) competence, the belief that one can interact effectively with one’s environment; and (iii) relatedness, perceptions of connectedness with significant others.

SDT also outlines two broad dimensions of motivation. Controlled motivation exists when students participate because they feel external pressure (e.g., from a teacher) or internal pressure (e.g., guilt) to participate. In contrast, students who have autonomous motivation towards PE participate because of the enjoyment or interest inherent in lessons, or because they value the outcomes of PE participation. In the context of PE, there is evidence that when teachers use motivational strategies that satisfy these three psychological needs, students experience more autonomous motivation and less controlled motivation. Importantly, autonomous motivation is positively associated with multiple adaptive outcomes [32], including student effort [19] and PA [16, 33] during lessons.

Motivational strategies that support students’ needs include, but are not limited to: (i) providing task choice and offering opportunities for students to take initiative; (ii) providing a rationale and explaining the personal relevance of an activity; (iii) acknowledging students’ difficulties when learning skills; and (iv) praising students for effort and improvement. A recent meta-analysis of randomized controlled trials (RCTs) [34], showed that these strategies can be taught effectively to a range of professionals (e.g., teachers, managers, healthcare workers), with teachers showing the greatest propensity to increase their supportive behaviors (pooled effect size *d* = 1.2). Research has also shown that using these instructional strategies is associated with greater student psychological needs satisfaction, leading to greater well-being, learning, and psychological development [19, 31, 35].

#### Previous physical education interventions based on self-determination theory

A number of recent studies have examined the effects of SDT-based interventions designed to promote needs supportive teaching in PE. For example, Tessier and colleagues [36] found that ratings by blinded observers across an eight-week period showed that teachers (*n* = 2) in the experimental condition were more needs supportive than teachers in the control condition. Another study [20] showed that teachers in the experimental condition (*n* = 5) who had been taught to use four needs supportive strategies showed greater increases in student ratings of support than teachers in the comparison condition (*n* = 5) who had only been taught two needs supportive strategies. The experimental group students also reported greater increases in autonomous motivation toward PE and more self-reported leisure-time PA than control participants. A third study [21], found that a SDT-based training intervention for teachers produced improvements in students’ needs satisfaction, autonomous motivation, and intention to be physically active during leisure time. Finally, in a study involving a single teacher, Perlman [14] found that students taught using a needs supportive teaching style were more physically active during lessons than when this teacher did not employ these strategies.

While the results of these studies are promising, a number of important limitations exist. These include: (i) evidence regarding the influence of needs supportive interventions on students’ PA during PE lessons has been limited to studies involving a small number of teachers [14] and those examining a limited range of needs supportive behaviors [22]; (ii) the lack of objective measurement of leisure-time PA, as only self-report measures have been employed [20]; and (iii) the limited assessment of the longer-term effects of these interventions [37].

### The current study

Few studies have been conducted with adolescents, but numerous studies have shown that interventions designed to improve primary and middle school PE teachers’ lesson planning and delivery can increase the MVPA that students accumulate during PE lessons [3]. These interventions have provided greater opportunities for MVPA during lessons, but little focus has been placed on enhancing students’ motivation towards PE in order to increase MVPA during lessons. Indeed, the content of many of these PA-focused interventions was designed to be enjoyable [10], but none of these interventions have been firmly grounded in relevant behavior change theory, nor have they examined whether the theoretical mediators were responsible for intervention effects on MVPA during PE lessons [3].

Theory-based interventions are needed in the PA promotion field [38–40], as they provide greater understanding of the process of behavior change and may ultimately lead to more effective interventions [41]. Self-determination theory provides a useful framework for physical activity behavior studies and an increasing number of interventions are based on SDT tenets [29, 34].

In this study, we will test a professional development intervention for teachers that combines the lesson planning and delivery approach [3] with motivational strategies designed to promote students’ needs satisfaction and autonomous motivation towards PE [20, 21]. A cluster RCT design, with allocation at the school level, was preferred to a RCT with individual level allocation because the risk of contamination effects would be high if teachers and students were randomly assigned from within a single school.

#### Web-based delivery

Previous research aimed at increasing students’ MVPA during PE has focused almost exclusively on teacher professional development conducted in face-to-face workshops [3]. While many of these interventions have produced significant and important increases in student MVPA, large-scale dissemination of exclusively ‘in-person’ professional development to teachers is logistically challenging and expensive. These challenges may constrain training to a single face-to-face workshop, which likely limits teachers’ learning and their implementation of new teaching strategies into their practice, compared with professional development delivered over an extended period of time. By capitalizing on the advantages of web-mediated professional learning, widespread reach, cost-effectiveness, and quality assurance (e.g., extending training over several sessions vs one longer session) may be achieved [42]. Thus, we designed a teacher professional development intervention that incorporates a ‘blended design’, with a mix of face-to-face and online learning.

#### Research questions

What effect does the intervention have on students’ MVPA during PE lessons (primary outcome)?What effect does the intervention have on secondary outcomes? vigorous intensity PA during PE lessons, moderate intensity PA during PE lessons, sedentary time during PE lessons leisure-time MVPA, as well as moderate and vigorous physical activity measured sperately, leisure-time sedentary behavior, student needs satisfaction and motivation towards PE, student motivation towards leisure-time PA physical self-concept and subjective well-being,student engagement during academic lessons following PE lessons,
To what extent do changes in the mediating variables (see Fig. 1) explain changes in outcomes?

**Fig. 1 Fig1:**
[figure not shown]
Promoting moderate-to-vigorous physical activity during physical education lessons and leisure time: a theoretical model based on self-determination theory

#### Hypotheses

We hypothesize that, compared with students in the control condition, students whose teacher participates in the intervention will be:Be more active during PE lessons (i.e., greater proportion of lesson time spent in MVPA, as well as moderate PA and vigorous PA measured separately).Spend a lower proportion of PE lessons being sedentary.Report greater needs satisfaction in PE, as well as higher autonomous motivation and lower controlled motivation and amotivation towards PE and leisure-time MVPA.Accumulate more MVPA and less sedentary time during leisure time (i.e., outside of school).More engaged in academic lessons that follow PE lessons.Report greater physical self-concept and subjective well-being.

We also hypothesize that intervention effects:7.On MVPA and sedentary behavior during PE lessons will be mediated by changes in student autonomous motivation and psychological needs satisfaction as well as teacher behavior that provides opportunities for students to engage in MVPA.8.On MVPA behavior during leisure time will be mediated by changes in autonomous motivation towards leisure-time MVPA.9.On student engagement in academic lessons will be mediated changes in MVPA they accumulated during the preceding PE lesson.10. On physical self-concept and subjective well-being will be mediated by changes in overall levels of MVPA accumulated.

## Methods

### Design

The trial will take place in government-funded secondary schools in the Western Sydney region of Australia, one of the fastest growing areas in the nation. This region has a large proportion of youth who come from low socio-economic status (SES) and immigrant backgrounds [43, 44], meaning they are at greater risk of physical inactivity compared with the Australian average [45].

This will be a two-arm, cluster randomized controlled trial with allocation at the school level (1:1 ratio to intervention and control conditions). See CONSORT flow diagram (Fig. 2). School years in Australia run from the end of January to the middle of December, with a summer break from mid-December to late January. Assessments will be completed at baseline of the first year (Term 1, February-April) and post-intervention (Term 4, September-December 2014: 7–8 months after baseline), which is the primary endpoint for this trial. A maintenance phase assessment will be conducted 14–15 months after baseline (Term 2, May–July).

**Fig. 2 Fig2:**
[figure not shown]
CONSORT flow diagram

### Participants

#### Schools inclusion criteria

In order to participate in the study, schools will need to meet the following inclusion criteria: (i) Secondary school with students enrolled in Years 8 and 9; (ii) Funded by the New South Wales (NSW) Department of Education; (iii) Located in the Western Sydney or Southwestern Sydney regions, as defined by the NSW Department of Education boundaries (http://www.schools.nsw.edu.au/schoolfind/locator/); (iv) Located in a postcode with low socioeconomic status, as defined by a decile rank of ≤ 5 according the Australian Bureau of Statistics’ Index of Relative Socioeconomic Disadvantage; and (v) Permission granted by the Principal, the Head Teacher of PE and at least one Year 8 PE teacher.

#### Teachers inclusion criteria

All PE teachers in participating schools, not only those who teach Year 8 during the main portion of the intervention, will be eligible to participate in the intervention. Including teachers from other year groups is intended to help ensure that when students move to Year 9 during the maintenance phase of the study, they will be taught by teachers who have completed the intervention training. Teachers who join the PE staff after the intervention will be invited to attend specially scheduled face-to-face sessions during which content will be taught.

#### Student inclusion criteria

All students enrolled in Year 8 PE classes in participating government-funded (NSW Department of Education) secondary schools in the Western Sydney region of NSW. Parental consent and student assent to participate will be obtained.

#### Student exclusion criteria

Students unable to participate in PE lessons (e.g., due to medical issues). Students who do not provide assent or did not receive parental consent to participate in the study will be excluded from assessment procedures, but will participate in PE lessons.

Human research ethics approval has been obtained from the Western Sydney University (H9171), Australian Catholic University (2014185 N) and the NSW Department of Education (2013162).

### Sample size

Sample size calculations were based on estimated effect sizes for the primary outcome. A recent meta-analysis [3], indicated that lesson planning and delivery interventions have a pooled effect of *d* = 0.60 on MVPA during PE lessons. To ensure 80 % power to detect an effect of this size would require 90 participants in a non-clustered trial (two-tailed probability level of 0.05). We considered the clustered nature of the data, including both school and class levels [46]. However, results from recent studies of MVPA in PE lessons indicated that clustering at the school level was negligible after accounting from clustering at the class level [22, 33]. As a result, we adjusted our sample size calculations for clustering using the formula 1 + (*m*-1)ρ, where *m* is the number of students per class and ρ is the intra-class correlation (ICC) [46].

Our recent study in Sydney-area schools indicated a class-level ICC of 0.62 [22], which was similar to Aelterman et al. [33] who reported a class-level ICC of 0.63. With an estimated class size of 22 participating students, an adjustment of 14.23 was required: 1 + (22–1)*0.63 = 14.23. Multiplying by the 90 participants required in non-clustered trial, we estimated that 1280 students would need to participate to achieve 80 % power. We estimate that 14 schools, with a mean of 4.5 classes of Year 8 students per school can be recruited and, therefore, aim to recruit 1386 students (14 schools × 4.5 classes per school × 22 students per class). Potential loss to follow up of up to 30 % of participants (*n* = 384; a very conservative estimate) will not substantially impact on the statistical power of the study. This resilience to loss of power exists because this study will use generalized mixed models, enabling the inclusion of all participants (included at baseline) in the analyses. In non-clustered longitudinal clinical trials, this analytic approach has been shown to yield similar point estimates and smaller decreases in statistical power than multiple imputations [47, 48].

### Blinding

Trained research assistants who will be blinded to school allocation will conduct baseline, post-intervention and maintenance phase assessments. Students participating in the study will also be blinded to hypotheses and school allocation. Teachers will be aware of their allocation to the intervention or control condition.

### Recruitment and randomization

Principals and Head Teachers of PE from all secondary schools that meet our eligibility criteria will be invited to express their interest in participating in this study. From the schools that indicate an interest in the study, we will attempt to purposively select schools in order to ensure that the sample is representative of the region’s population, in terms of school size and gender composition (i.e., single sex or co-educational). Schools that agree to participate will be match paired according to SES of the postcode in which the school is located (according to the Index of Relative Socio-Economic Disadvantage:), school size (Year 8 enrolment), gender composition of PE classes (i.e., single sex vs co-ed) and the duration of PE lessons. Using a computer-based randomization plan generator, the 14 schools will be randomized to the control or intervention condition from within each pair following baseline assessments. A researcher not associated with recruitment or data collection, and who will be blind to school identity, will carry out randomization procedures.

All PE teachers in schools that enter the trial will be invited to an information session during which study procedures will be outlined and questions answered. The research team will present study information and provide an information letter and consent form to all Year 8 students from classes whose teacher agrees to participate.

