### Statistical analysis

Between-arm differences in changes on the primary and secondary outcomes will be analyzed using generalized linear mixed models according to intention-to-treat and per-protocol principles. Specifically, intention to treat analyses will involve analysis of outcomes collected from all students who completed baseline assessment, regardless of whether or not they complete post-intervention or maintenance phase assessments. Between-arm differences in changes on the primary and secondary outcomes will be assessed by including an indicator variable for group allocation (arm), a variable representing time (baseline, post-intervention, and/or maintenance) and their interaction.

For the primary outcome (MVPA during lessons), student data will be gathered from between one and three lessons per student at each of the time points (baseline, post-intervention and maintenance). The repeated measure will be modeled as a random intercept effect. Lesson will also be modeled as a random intercept effect. Analyses will also be adjusted for class and teacher clustering-each teacher will be given a case ID. In instances where teachers ‘team-taught’ (i.e., two teachers within a single lesson), we will create a new case ID that is unique to that combination of teachers. In some instances students will be taught by different teachers within a time point (i.e., from lesson to lesson) or across time points (e.g., from baseline to post-intervention). We will account for this data structure by specifying cross-classified random effects models. Possible school-level residual clustering will be explored and included in the models, if appropriate. In sum, we will include four random intercept effects: (i) lesson; (ii) student; (iii) teacher; and (iv) class. We will consider a fifth random intercept effect for school, if preliminary analyses suggest clustering of MVPA during lessons at the school level.

We will also control for a number of variables that could influence students’ MVPA during lessons. These include temperature at the start time of the lesson, the type of activity included in the lesson and the timing of accelerometer fitting for the lesson (the student arrived at lesson wearing an accelerometer or was fitted at started of lesson).

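### Schools are randomised within seven matched pairs, but the stated primary model has neither the pair nor any matching factor, and has school only conditionally

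*Protocol article*

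**What the plan says.** Recruitment and randomization: "Schools that agree to participate will be match paired according to SES of the postcode in which the school is located". The other matching factors are Year 8 enrolment, whether PE classes are single-sex or mixed, and the length of PE lessons. After baseline assessment, one school in each pair goes to each arm, so 14 schools form 7 pairs.

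Statistical analysis: the treatment effect is the arm-by-time interaction. The section sums up its random part as intercepts for lesson, student, teacher and class. A school intercept is a possible fifth, dependent on preliminary analyses. On covariates it says "We will also control for a number of variables that could influence" lesson MVPA, and names temperature, activity type and when the accelerometer was fitted. No pair term and no matching factor is named. Socio-economic status and gender appear only as exploratory moderators.

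Sample size: the calculation corrects for class clustering alone, treats residual school clustering as negligible, and takes no credit for matching.

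**The concern.** When allocation is restricted within pairs, the restriction belongs in the analysis, either directly or through the factors that formed the pairs. Otherwise any between-pair variation that the design removed from the arm difference can stay in its estimated error.

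The investigators evidently regard the four factors as prognostic, since they matched on them. Lesson duration is a good example: the outcome is a proportion of bell-to-bell time, so fixed changing and set-up time plausibly takes a larger share of a short lesson.

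With only 14 randomised units, how the school level is handled affects both the error rate and the precision of the primary comparison. The plan leaves that to a look at the data.

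**Working it through.** **1. The plan's own figures.** Inputs from Sample size: "two-tailed probability level of 0.05", 80% power, and the statement that "lesson planning and delivery interventions have a pooled effect of" d = 0.60. A two-sample t-test needs 44.6, so 45 per arm, which agrees with "would require 90 participants in a non-clustered trial". For clustering the section relies on a study "who reported a class-level ICC of 0.63". The design effect is 1 + 21 × 0.63 = 14.23, as in "With an estimated class size of 22 participating students, an adjustment of 14.23 was required". Then 90 × 14.23 = 1280.7, which agrees with "we estimated that 1280 students would need to participate to achieve 80 % power". The target is 14 × 4.5 × 22 = 1386. All reproduce, and none depends on the matching.

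**2. Set-up for the standard error.** Take total variance 1, with class and school together holding 0.63, and 4.5 classes of 22 (99 students) per school. Two quantities are not in the document and are assumed:
- s, the school share of total variance: 0 to 0.10.
- p, the part of that share explained by the pairing: 0 to 0.75.

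Variance of a school mean: V = s + (0.63 − s)/4.5 + 0.37/99.

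True variance of the arm difference under paired allocation: (2/7)(V − sp).

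**3. School term kept, pair omitted.** The model estimates (2/7)V, so the SE ratio is √[V/(V − sp)].
- s = 0.05: V = 0.05 + 0.1289 + 0.0037 = 0.1826. At p = 0.3, √(0.1826/0.1676) = 1.04. At p = 0.5, √(0.1826/0.1576) = 1.08.
- s = 0.10: V = 0.10 + 0.1178 + 0.0037 = 0.2215. At p = 0.3, √(0.2215/0.1915) = 1.08. At p = 0.5, √(0.2215/0.1715) = 1.14.
- Extreme case, s = 0.10 and p = 0.75: 1.23.

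Simulated type I error (40,000 runs, tests on school means) is 0.050 with s = 0, 0.037 at s = 0.05 and p = 0.5, and 0.021 in the extreme case. This branch is conservative.

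**4. Default model, no school term.** Treating classes as the independent units, the model expects a variance of [2/(7 × 4.5)] × [(0.63 − s) + 0.37/22 + s(1 − 3.5/30.5)].
- s = 0: ratio to the true SE 1.00, type I error 0.050.
- s = 0.05, p = 0.5: (2/31.5) × 0.6411 = 0.0407, against a true (2/7) × 0.1576 = 0.0450. Ratio 0.95, type I error 0.062.
- s = 0.10, p = 0: (2/31.5) × 0.6353 = 0.0403, against (2/7) × 0.2215 = 0.0633. Ratio 0.80, type I error 0.116.

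The ratio does not exceed 1 anywhere in the assumed range. At s = 0.10 it would pass 1 only where (2/7)(0.1215 + 0.10(1 − p)) falls below 0.0403, which needs p above about 0.80.

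**5. The price of a strict paired test.** Degrees of freedom fall from 12 to 6, and the critical t rises from 2.179 to 2.447. Simulated power for d = 0.6:

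| s | p | paired (6 df) | school, no pair (12 df) |
|---|---|---|---|
| 0 | – | 0.68 | 0.77 |
| 0.05 | 0.5 | 0.65 | 0.68 |
| 0.10 | 0.5 | 0.61 | 0.59 |
| 0.10 | 0.75 | 0.68 | 0.61 |

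**6. Limits.** These calculations use one time point and cluster means, not the full cross-classified model. Stable school and pair differences in level largely cancel from an arm-by-time contrast. Only variation in change that follows school or pair remains, so the effects there would be smaller.

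**The case against.** The best defence has four parts.

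- **Breaking the pairs can be legitimate.** With seven schools per arm and school clustering retained, an unpaired analysis is valid, usually conservative, and more powerful when pairing is weak. The plan's view that school clustering is negligible puts it near that case. This stands, and it argues against a strict paired test. It does not argue against covariate adjustment or a random pair effect, and the plan neither states nor justifies a decision to break the pairs.
- **The contrast is a change.** This stands and reduces the size of the effect.
- **The article is condensed.** The covariate list is worded openly, and an analysis plan not shown could add terms. This stands in part. The random effects, however, are summed up as a definite list, in a section detailed enough to define identifiers for team-taught lessons.
- **Matching still does its work at allocation.** A reader might infer that leaving it out of the model wastes it. It does not: the arms remain balanced on the four factors.

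A reader might also take the named covariates to be purely post-randomisation variables. They belong to lessons at every assessment, baseline included, and randomisation follows baseline, so some values precede it.

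**Conclusion.** The mismatch between design and stated model is real. Randomisation is within pairs, while the model carries neither the pair nor a matching factor, and school only conditionally.

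Its consequence is modest and has no single direction. With a school term and informative pairing, the SE is about 4% to 14% too wide at s = 0.05 to 0.10 and p = 0.3 to 0.5, and less for arm by time. Without a school term, the SE is correct or too narrow across the assumed range, with type I error up to 0.116. Both s and p are assumptions, because the document gives neither.

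Two stronger readings are not supported. The first is that the error bars are simply too wide: that requires a school term, which the default model lacks. The second is an inflation of 20% to 41%. Those figures are 1/√(1 − 0.3) = 1.20 and 1/√(1 − 0.5) = 1.41, and they treat the matched share as a share of the whole variance of a school mean. Here much of that variance comes from classes within schools, which explaining school variance cannot remove. Even perfect matching on school variance gives a within-pair correlation of at most 0.05/0.183 = 0.27 at s = 0.05, and 0.10/0.2215 = 0.45 at s = 0.10.

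**What to change.** State in advance how the matching enters the primary model, by one of two routes:

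- Adjust for the matching factors: lesson duration and single-sex or mixed status at lesson or class level, postcode SES and Year 8 enrolment at school level. Add their interactions with time where arm by time is the estimand.
- Or include a random pair effect with pair-by-time.

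Under either route, keep school in the model as the randomised unit, with small-sample degrees of freedom, and do not make it depend on a preliminary look. Report a within-pair permutation test over the 2^7 = 128 possible allocations as a sensitivity check; its smallest two-sided p-value is 2/128 = 0.016. A strict paired test on 6 degrees of freedom is not recommended as the primary analysis, because it loses power when pairing is weak.

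The cost is a change of wording before analysis, since the matching data are already held for the randomisation. The downside is a few school-level degrees of freedom.
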